**Methods:**

This study is a two-arm cluster-randomized trial that will be carried out in urban health centers in Spain. We will recruit 160 people aged between 65 and 80 without cardiovascular disease or cognitive impairment (score in the Mini-mental State Examination ≥24). On a visit to their center, intervention group participants will be instructed to use a smartphone application for a period of 3 months. This application integrates information on physical activity received from a fitness bracelet and self-reported information on the patient’s daily nutritional composition. The primary outcome will be the change in the number of steps measured by accelerometer. Secondary variables will be adherence to the Mediterranean diet, sitting time, body composition, quality of life, independence in daily living activities and cognitive performance. All variables will be measured at baseline and on the assessment visit after 3 months. A telephone follow-up will be carried out at 6 months to collect self-reported data regarding physical activity and adherence to the Mediterranean diet.

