### Sample size calculation

The sample size was estimated for the main variable of the study (Physical activity - steps/day). Assuming a standard deviation of 3847 steps/day [49], a power of 0.8 and an alpha risk of 0.05 in a bilateral test, 80 participants are necessary in each group to detect an increase of 1850 steps/day in the experimental group compared to the control group. This calculation was based on the estimate by Alonso-Dominguez et al. [50]. We assumed a dropout rate of 15% throughout the duration of the study (3 months).

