### Analysis of the effect of the intervention on primary (steps/day) and secondary outcomes

To analyze the changes at 3 and 6 months’ post-baseline in the primary (physical activity - steps/day) and the secondary outcome within the same group, the Student’s t-test or the Wilcoxon test will be used for paired data. The McNemar test will be used for dichotomous variables.

The intervention effect will be analyzed by comparing the changes between IG and CG in blood pressure and secondary variables by using ANCOVA and adjusting for possible confounders. The intervention effect over the period studied will be measured by a repeated measures analysis.

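### The between-arm ANCOVA names blood pressure, which the trial does not measure, where the primary outcome, steps/day, should stand

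*Protocol article*

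**What the plan says.** The abstract fixes the primary outcome: "The primary outcome will be the change in the number of steps measured by accelerometer". The sample size section uses the same variable: "The sample size was estimated for the main variable of the study (Physical activity - steps/day". The section headed as the analysis of the intervention's effect on primary (steps/day) and secondary outcomes then does three things.

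- It assigns paired tests to changes inside each group, for the primary and the secondary outcomes: the Student's t-test or, failing that, "the Wilcoxon test will be used for paired data".
- It assigns the comparison of the arms to a different set of variables: "The intervention effect will be analyzed by comparing the changes between IG and CG in blood pressure and secondary variables by using ANCOVA", with the model "adjusting for possible confounders".
- It adds a repeated measures analysis of the intervention effect, without naming an outcome or a model.

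Under General analysis, a two-group t-test or Mann-Whitney U test is listed with no outcome attached, and intention-to-treat is stated for the main and secondary variables.

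**The concern.** The sentence that says how the intervention effect will be estimated names a variable that the trial does not collect, in the place where the primary outcome belongs. Read literally, the adjusted IG-CG comparison covers an unmeasured variable and the secondary outcomes, but not steps/day. The method that the section does attach to steps/day, a before/after test within each arm, does not compare the arms. Both arms receive counseling on diet and physical activity, so both may improve, and separate paired tests cannot show whether one improved more than the other.

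The primary analysis is where a reader most needs to see that outcome, model and adjustment were fixed in advance. As printed, none of the three is tied to steps/day.

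**Working it through.** **1. Is blood pressure a variable of this trial?** It would have to appear in one of these places:

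| Place in the protocol article | Variables named | Blood pressure? |
|---|---|---|
| Hypothesis and objective | physical activity, Mediterranean diet; then body composition, quality of life, daily living, cognition | no |
| Abstract, Methods | steps (primary); diet, sitting time, body composition, quality of life, daily living, cognition | no |
| Table 1 | accelerometer, IPAQ, Marshall, MEDAS, impedance, cognitive tests, Pfeffer, WHOQOL-AGE, EQ-5D | no |
| Primary outcome to Other variables | the same, plus motivation and app adherence | no |
| Sample size calculation | steps/day | no |
| Effect-of-intervention section, ANCOVA sentence | blood pressure and secondary variables | **only here** |

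**2. Does another passage give steps/day an adjusted between-arm analysis?**

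- General analysis: the two-group test is unadjusted and names no outcome. It could be applied to steps/day, but it does not say whether changes or 3-month values are compared.
- The intention-to-treat sentence gives an analysis principle, not a test.
- The repeated measures sentence names no outcome. Table 1 has the accelerometer at baseline and 3 months only, so steps/day has two time points.
- Secondary analyses: the regression on physical activity changes looks for influential variables. It is not presented as the estimate of the arm effect.

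None of them does.

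**3. The plan's own figure.** The inputs are all in Sample size calculation: SD 3847, 80% power, two-sided alpha 0.05 and 15% dropout. The target is stated as: "80 participants are necessary in each group to detect an increase of 1850 steps/day in the experimental group compared to the control group".

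n per arm = 2 × (1.960 + 0.842)² × (3847 / 1850)² = 67.9, so 68. Allowing for dropout, 68 / (1 − 0.15) = 80.

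The stated 80 per group reproduces. This is an unadjusted between-arm calculation for steps/day, so the trial was sized for the comparison that the ANCOVA sentence fails to name.

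**4. What the choice of model is worth (illustration only).** Two assumptions are not in the document: that 3847 is the SD of step levels in each arm, and a correlation r between baseline and 3-month steps. With 68 completers per arm and a difference of 1850, power is from the two-sided t-test at 0.05.

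- Unadjusted 3-month values: SD 3847, d = 1850 / 3847 = 0.481, power 79.5%.
- ANCOVA on baseline: SD = 3847 × √(1 − r²).
- Unadjusted change score: SD = 3847 × √(2(1 − r)).

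| r | ANCOVA SD | ANCOVA power | Change-score SD | Change-score power |
|---|---|---|---|---|
| 0.3 | 3670 | 83.1% | 4552 | 65.3% |
| 0.5 | 3332 | 89.5% | 3847 | 79.5% |
| 0.7 | 2747 | 97.4% | 2980 | 94.9% |

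The candidate analyses of steps/day are therefore not interchangeable. At r = 0.3, moving from the change-score test to ANCOVA raises power from about 65% to 83%.

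**The case against.** The intended meaning can be recovered. The section heading covers the primary outcome (steps/day), and the ANCOVA sentence sets blood pressure beside the secondary variables, exactly where the primary outcome would stand. The paired tests are described as changes within a group, while the term intervention effect is kept for the comparison of arms. General analysis supplies a two-group test, and the sample size is for a difference between arms. All of this stands.

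A reader might infer that the trial plans no between-arm comparison of steps, or that its main claim will rest on a significant paired test in one arm and a non-significant one in the other. The documents do not support either inference.

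A reader might also infer that the open covariate list lets the analyst choose a favourable model after unblinding. The Blinding section says that the statistical analyst will not know the participants' groups, so that argument fails. A full covariate list is also something that a condensed article may leave to an analysis plan that is not shown.

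Finally, a misnamed variable costs no power in itself, and the illustration depends on an assumed correlation. That is correct, and it is why the power figures do not measure the size of the error.

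What remains is that the document states the method and states it wrongly, for the endpoint that matters most. A separate analysis plan can add detail to a sentence, but it does not make a wrong endpoint right.

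**Conclusion.** The point holds as an error of specification. The only adjusted between-arm analysis in the protocol article is written for a variable that the trial does not measure, and the primary outcome is not named in it. The absence of blood pressure elsewhere can be checked directly and rests on no assumption. The intended comparison is clear from the rest of the document, so this is a sentence to correct, not a gap in the design.

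The sample size of 80 per group is unaffected. The gain from baseline adjustment, from about 79.5% to between 83% and 97% power for r from 0.3 to 0.7, depends on the assumed correlation and on reading 3847 as the SD of levels. It supports naming baseline steps/day in the model and nothing more.

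**What to change.** Correct the ANCOVA sentence along these lines: *The primary analysis is the IG-CG difference in 3-month accelerometer steps/day, estimated by ANCOVA adjusted for baseline steps/day and reported with a 95% confidence interval. Each continuous secondary outcome is analysed by the same model with its own baseline value.* Remove blood pressure. Keep adjustment for any other confounders as a sensitivity analysis, and label the within-group paired tests descriptive.

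Do not add health center as a fixed covariate yet. The abstract calls the trial cluster-randomized, while Trial design and Randomization describe participants being allocated in three centers. If whole centers were allocated, a fixed center effect would be confounded with arm. Those passages need reconciling first.

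The cost is a change of wording. Baseline and 3-month accelerometer data are already planned for every participant, and the sample size does not change.

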### Data collection / outcomes

Each participant will undergo a baseline assessment and a follow-up evaluation at 3 months. Some variables (self-reported physical activity and adherence to the Mediterranean diet) will also be collected in a follow-up phone call at 6 months. The information generated by the app during the intervention period (physical activity and food) will also be analyzed. An overview of data collection is presented in Table 1.

**Table 1 Tab1:** Timeline of measures

Measure	Baseline	3 months	6 months
Accelerometer	X	X	
International physical activity questionnaire (IPAQ)	X	X	X
Marshall questionnaire- sitting time	X	X	X
Mediterranean diet screener (MEDAS)	X	X	X
Body composition- impedanciometer	X	X	
Mini-Mental State Examination, the clock drawing test and categorial fluency	X	X	
Pfeffer questionnaire	X	X	
WHOQOL-AGE	X	X	
EuroQoL 5-D (EQ-5D)	X	X	

*IPAQ* International physical activity questionnaire, *MEDAS* Mediterranean diet adherence questionnaire, *WHOQOL-AGE* World health organization quality of life age questionnaire

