### Primary outcome

#### Physical activity

The main physical activity variable will be the change in the amount and intensity of physical activity expressed in steps/day, measured by accelerometer. This device also calculates the total time spent daily in light, moderate and intense physical activity and the kilocalories used. Validated GT3X accelerometers will be used [53]. Participants will wear the accelerometer strapped to the right side of their waist with an elastic belt for seven consecutive days. Data will be recorded minute by minute. If the accelerometer records 10 consecutive zeros over the course of 10 min, the measurement will be considered null. The intensity of physical activity (low, moderate or high) will be determined according to the cut points proposed by Freedson [54]. Physical activity will also be measured by self-report using the International Physical Activity Questionnaire (IPAQ). The short version will be used, which is validated in Spanish and assesses physical activity over the last 7 days [55]. This questionnaire classifies adult populations by their level of activity (low, moderate and high) and differentiates three types of activity: walking, moderate activity and vigorous activity. The physical activity dose will be estimated in METs/minute/week. An active person is considered to be someone who performs at least 30 min of moderate activity, five days a week, or at least 20 min of vigorous activity, three days a week, or reaches 450 METs/minute/week.

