### Analysis plan

#### General analysis

Results will be expressed by means and standard deviations for quantitative variables, or by frequency distributions and percentages in the case of qualitative ones. The normality of variables will be tested by means of the Kolmogorov-Smirnov test. When a normal distribution cannot be assumed, we will use the corresponding nonparametric tests. The chi-square test or Fisher’s exact test will be applied to analyze the association between independent qualitative variables. Using the Student’s t-test or the Mann-Whitney U test, the means between the two groups will be compared. The relationship between quantitative variables will be analyzed with the Pearson or Spearman correlation coefficients.

Analysis of the results for the main variable and the secondary variables will be carried out by intention-to-treat. In addition, app adherence will be the subject of a secondary analysis, as described in the results of the EVIDENT II study [66] (< 60 days and > 60 days), and other relevant subgroups will also be analyzed in terms of their physical activity or previous adherence to the Mediterranean diet.

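### The plan does not secure the outcome's own baseline value as a covariate in the between-arm comparison; if it is left out, about 10 points of power on steps/day are at risk at an assumed correlation of 0.5

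*Protocol article*

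**What the plan says.** Under Data collection / outcomes, the protocol article states: "Each participant will undergo a baseline assessment and a follow-up evaluation at 3 months". Table 1 there lists accelerometry and every secondary measure at both visits. The primary outcome is defined under Physical activity: "The main physical activity variable will be the change in the amount and intensity of physical activity expressed in steps/day, measured by accelerometer".

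Two places describe how the arms are compared.

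- General analysis gives a generic rule: "Using the Student’s t-test or the Mann-Whitney U test, the means between the two groups will be compared".
- Analysis of the effect of the intervention on primary (steps/day) and secondary outcomes says that the changes in the two arms will be compared in blood pressure and "secondary variables by using ANCOVA and adjusting for possible confounders". It then announces a repeated measures analysis without detail.

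No covariate is named in either place. The outcome's baseline value is neither listed nor excluded. Baseline lifestyle appears under Analysis by subgroups, but only as a possible effect modifier.

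**The concern.** Randomization removes confounding in expectation. What earns a covariate its place in the between-arm model is how well it predicts the outcome, and the baseline value of the same measure is usually the strongest predictor available. A rule framed around confounders does not point to it: a baseline step count that is highly prognostic but happens to be balanced would not look like a confounder.

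Comparing changes does not do the same job. A change score fixes the coefficient of baseline at 1. With equal variances at the two visits, the most precise coefficient is the baseline–follow-up correlation, which is below 1. If baseline is omitted, two things follow:

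- the treatment effect is estimated less precisely;
- in the trial actually run, the arm that starts lower by chance tends to show the larger increase, through regression to the mean.

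The argument applies equally to diet score, sitting time, body composition, cognition and quality of life.

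**Working it through.** **Inputs from Sample size calculation.** "Assuming a standard deviation of 3847 steps/day [49], a power of 0.8 and an alpha risk of 0.05 in a bilateral test", "to detect an increase of 1850 steps/day in the experimental group compared to the control group", 80 participants per group, 15% dropout. The article does not say whether 3847 is the SD of one measurement or of the change, and it gives no baseline–follow-up correlation. The correlation, ρ, is therefore an assumption, shown from 0.3 to 0.8. Individual randomization and equal variances at the two visits are also assumed.

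**Step 1: reproduce the plan's figure.** n per arm = 2 × (1.96 + 0.8416)² × (3847/1850)² = 67.9, so 68. Then 68/0.85 = 80, as stated. The sample size is an ordinary two-sample calculation with no baseline adjustment.

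**Step 2: residual SD with and without baseline.**

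- If 3847 is a single-time SD: SD of change = 3847 × √(2(1 − ρ)); residual SD with baseline as covariate = 3847 × √(1 − ρ²).
- If 3847 is the SD of change: SD without baseline = 3847; residual SD with baseline = 3847 × √((1 + ρ)/2).

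At ρ = 0.5 the two readings coincide: 3847 without baseline and 3847 × √0.75 = 3332 with it, a 25% cut in variance.

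**Step 3: power** (noncentral t, 68 per arm, difference 1850, two-sided 0.05).

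| ρ | Single-time SD: change score | Single-time SD: with baseline | SD of change: without baseline | SD of change: with baseline |
|---|---|---|---|---|
| 0.3 | 65.3% | 83.1% | 79.5% | 93.2% |
| 0.5 | 79.5% | 89.5% | 79.5% | 89.5% |
| 0.6 | 87.5% | 93.6% | 79.5% | 87.5% |
| 0.7 | 94.9% | 97.4% | 79.5% | 85.5% |
| 0.8 | 99.3% | 99.6% | 79.5% | 83.5% |

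Under the single-time reading the difference runs from about 18 points (ρ = 0.3) through 10 (ρ = 0.5) to under half a point (ρ = 0.8). Under the SD-of-change reading it runs from about 14 points to 4. A normal approximation gives nearly the same result at ρ = 0.5: 80.1% against 89.9%.

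**Step 4: chance imbalance.** With a single-time SD of 3847, one standard error of the baseline difference between arms is 3847 × √(2/68) ≈ 660 steps/day. Given a baseline difference d, the change-score estimate is shifted by −(1 − ρ) × d. For d = 660 and ρ = 0.5 the shift is 330 steps/day in size, or 330/1850 ≈ 18% of the target difference.

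**The case against.** The strongest reply is that nothing wrong has been stated. ANCOVA is named, ANCOVA commonly carries the baseline value, a comparison of changes is compatible with that, and baseline may be among the unnamed covariates. A condensed article may also leave its covariate list to a fuller document that is not shown. This stands in part. A reader might infer that 10 points of power are being given up. The text does not support that: it leaves baseline adjustment open, and the correlation of 0.5 is an assumption. What survives is that the article does state a criterion for choosing covariates, and that criterion does not lead to the baseline value.

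Three other inferences go too far.

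- **That the estimate is biased.** Participants are randomized, so a change-score contrast is unbiased over repeated randomizations. The 330 steps/day is a conditional shift for a given imbalance.
- **That the planned 80% power is undermined.** The sample size stands without adjustment if 3847 is the SD of change, or if it is a single-time SD and ρ is about 0.5 or more. A shortfall arises only under the single-time reading with a lower correlation, which the article does not establish.
- **That covariates will be picked by observed imbalance.** The confounder wording permits this, but nothing in the article says so.

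Two further points are fair. The t-test sits among general tools and is not designated as the test of the intervention effect. And the ANCOVA sentence names blood pressure, which is not an outcome in Table 1, while steps/day appears only in the section heading. That mismatch is a separate defect. The question of covariates is the same whichever outcome the sentence is meant to cover.

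**Conclusion.** The point holds as a low-cost improvement to the analysis wording. The article neither secures nor excludes baseline adjustment, and its stated covariate criterion is the wrong one for a randomized trial. The power at risk on steps/day if baseline is left out is about 10 points at ρ = 0.5, within the ranges tabulated above; it is negligible only if 3847 is a single-time SD and the correlation is high. These figures rest on 68 evaluable participants per arm, individual randomization, equal variances at the two visits and an assumed correlation. They do not show that power has been lost or that the trial is too small.

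**What to change.** In the section on the effect of the intervention on primary and secondary outcomes, replace the confounder clause with a statement along these lines: the between-arm effect on steps/day and on each quantitative secondary outcome is estimated by ANCOVA of the 3-month value (or the change) on group, with the baseline value of the same outcome as a fixed covariate; any further covariates are prespecified and not chosen by observed imbalance. Name this model as the source of the primary estimate and p-value, with the unadjusted t-test as supportive. Naming steps/day in that sentence also repairs its mismatch with the section heading.

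The cost is one sentence and one degree of freedom per model. No new data, visits or participants are needed. If baseline adjustment was always intended, the change simply records it.

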### Secondary analyses

Multiple multivariate regression analysis will be performed to identify the variables with the greatest influence on physical activity changes and the secondary variables analyzed.

All analyses will be carried out with SPSS version 23.0 (IBM Corporation, Armonk, NY, USA) and an alpha risk of 0.05 will be assumed as the limit for statistical significance.

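### No deciding between-arm analysis is fixed for steps/day: ANCOVA and repeated measures are both given, and the ANCOVA sentence names blood pressure instead of the primary outcome

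*Protocol article*

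**What the plan says.** All references are to the protocol article.

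- **Analysis of the effect of the intervention on primary (steps/day) and secondary outcomes.** Changes in the two arms are compared "by using ANCOVA and adjusting for possible confounders". The outcomes named in that sentence are blood pressure and the secondary variables; the confounders are not listed. The next sentence reads "The intervention effect over the period studied will be measured by a repeated measures analysis".
- **General analysis.** Under a general rule that names no outcome and no time point, "the means between the two groups will be compared" by Student's t-test or, where normality cannot be assumed, the Mann-Whitney test.
- **Secondary analyses.** For all analyses, "an alpha risk of 0.05 will be assumed as the limit for statistical significance". No order or adjustment is given.
- **Sample size calculation.** The trial is sized for a single comparison of steps/day, with "a power of 0.8 and an alpha risk of 0.05 in a bilateral test".
- **Table 1 (timeline of measures).** The accelerometer is used at baseline and 3 months only. IPAQ, sitting time and the Mediterranean diet screener are also collected at 6 months. Blood pressure does not appear in the table or in the outcome sections.

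**The concern.** The section whose heading names steps/day gives the same treatment effect to two models and does not say which one answers the primary question. The two can disagree. The only sentence prescribing ANCOVA does not mention the primary outcome, so it is unclear whether ANCOVA applies to steps/day at all.

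Two things are at stake. First, precision: the one model that unambiguously covers steps/day is the weaker of the two. Second, error control: the sample size rests on one two-sided test at 0.05, and that rate is secured only if one test is designated in advance.

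**Working it through.** **1. The plan's own figure.** The Sample size calculation gives SD 3847, difference 1850, two-sided alpha 0.05, power 0.80 and dropout 15%.

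n per arm = 2 × (1.960 + 0.842)² × (3847/1850)² = 2 × 7.849 × 4.324 = 67.9, so 68.
After dropout: 68 / 0.85 = 80.

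This matches the stated 80 per arm. It is the size for one two-group test.

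**2. What repeated measures amounts to for steps/day.** With two time points and two groups, the group-by-time F statistic is the square of the two-sample t statistic on change. The repeated measures analysis therefore adds no longitudinal information for steps/day. An unadjusted t-test on change would duplicate it exactly.

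**3. Efficiency.** Let ρ be the correlation between baseline and 3-month steps/day, with equal variance σ² at both times. The document does not give ρ, so 0.3-0.9 is assumed.

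- Variance of the between-arm difference in change: (2σ²/n) × 2(1 − ρ)
- Variance of the baseline-adjusted ANCOVA estimate: (2σ²/n) × (1 − ρ²)
- Ratio: (1 − ρ²) / [2(1 − ρ)] = (1 + ρ)/2

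The ratio is 0.65 at ρ = 0.3, 0.75 at 0.5, 0.85 at 0.7 and 0.95 at 0.9. ANCOVA is never worse, and the gain is largest where the correlation is low.

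**4. Type I error if any significant result could be claimed.** Trials were simulated with no effect, normal data, 68 completers per arm and 20,000 trials per setting. An error is counted when at least one test has p < 0.05.

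| ρ | ANCOVA alone | Repeated measures alone | Either of the two | Either, or t-test on 3-month values |
|---|---|---|---|---|
| 0.3 | 5.0% | 5.2% | 7.9% | 9.3% |
| 0.5 | 5.2% | 5.2% | 7.5% | 9.7% |
| 0.7 | 4.8% | 5.0% | 6.7% | 10.0% |
| 0.8 | 5.2% | 5.3% | 6.9% | 10.7% |
| 0.9 | 4.9% | 5.2% | 6.0% | 10.0% |

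The simulation standard error near 10% is √(0.10 × 0.90 / 20,000) = 0.2 percentage points. A repeat with 160,000 trials per setting gave 6.0-7.7% for the two analyses and 9.1-10.2% with the 3-month t-test, so the 10.7% is partly simulation noise.

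**5. Other readings of the text**, under the same any-result rule:

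- Repeated measures plus t-test on change: 5%, because they are one test.
- Repeated measures plus Mann-Whitney on change: about 6%.
- Repeated measures plus ANCOVA adjusted only for confounders that explain 5-20% of the variance in change: 6.0-7.4%.
- Repeated measures plus t-test on 3-month values, with no ANCOVA: 9.0-9.8%.

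**The case against.** The strongest reply is that the document nowhere says a significant result from any one analysis counts as success. A reader might infer that the plan itself raises the error rate for steps/day to 7-10%. The text does not support that: the figure needs an unstated decision rule and an assumed correlation. This objection stands in full.

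A reader might also count three separate primary tests. That goes too far. The t-test or Mann-Whitney sentence belongs to a general section and names no outcome. The two tests are alternatives, and a t-test on change coincides with repeated measures. The upper figures need an unadjusted test on 3-month values, although the primary outcome is defined as a change.

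Read literally, the ANCOVA sentence excludes steps/day and leaves only repeated measures for it in that section, at 5%. That reading is possible, but it fits badly with a heading that names steps/day and a sentence that names an outcome the trial does not list. It would also leave the primary outcome with the less efficient model.

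Repeated measures does have a proper role for outcomes collected at baseline, 3 and 6 months, and the fix keeps it there.

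Finally, ranking models and listing covariates is often left to an SAP, which may exist. That is fair as far as covariate detail goes. But the article is not silent here: it states two analyses of one effect and names the wrong outcome in one of them.

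**Conclusion.** The point holds as a matter of an unfixed primary analysis and a wrongly named outcome. The section gives two between-arm analyses at 0.05, fixes neither as deciding for steps/day, and writes blood pressure where the primary outcome would be expected.

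The firm part of the size is efficiency: baseline-adjusted ANCOVA has about 65-95% of the variance of the change-score test, given equal variances and a correlation of 0.3-0.9. The error-rate part is conditional. Type I error would be roughly 6-8% for the two analyses, and up to about 10% with a 3-month t-test, only if any significant result could be claimed. Each analysis taken alone keeps about 5%. The nominal tests are valid; what is missing is the statement of which one decides.

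**What to change.** In the section on the intervention effect:

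1. Replace blood pressure with steps/day in the ANCOVA sentence.
2. Name one deciding analysis: between-arm ANCOVA of steps/day at 3 months with baseline steps/day as covariate, two-sided 0.05. Using the change as the response with the same covariate gives the same treatment estimate.
3. Keep the repeated measures analysis for the outcomes measured at baseline, 3 and 6 months (IPAQ, sitting time, Mediterranean diet screener).
4. Label any other between-arm comparison of steps/day as supportive, with no claim resting on it.

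This takes a few sentences in the protocol or SAP and uses data already planned, with no extra participants or visits. The price is that the investigators give up the freedom to lead with a different model once results are known.
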